### Control group

Similar to the intervention group, the trained research assistant will first ask the subjects about the priority of engaging in any desirable health-related lifestyle practice and to state a targeted goal in which they perceive as the easiest to achieve after completing the baseline questionnaires. In addition, the subjects will be given a self-help smoking cessation booklet with a public quitline number. However, subjects in the control group will not receive brief MI and follow-up booster intervention.

### Data collection

#### Baseline

Before randomisation, the subjects will be invited to complete a structured questionnaire, administered by a trained research assistant face-to-face. This structured questionnaire will be developed through adopting or modifying international and/or locally validated instruments. The questionnaire will gather information including smoking and quitting history, stage of readiness to quit, utilization of existing smoking cessation services, and demographic information such as age, gender, and marital status. The clinical information will be obtained by the trained research assistant from the subjects’ medical records.

#### Follow-up

All subjects will receive follow-up telephone call at 1, 3, 6 and 12 months from our trained research assistant. In each telephone follow-up, the subjects will be asked to complete the structured questionnaire again. Subjects who are abstinent from cigarette use ≥7 days at 12-month follow-up will be invited for a biochemical validation. The biochemically validated 7-day point prevalence of abstinence will be confirmed by saliva cotinine level < 115 ng/ml in parallel test and a carbon monoxide level in expired air < 9 ppm (p.p.m.) [18]. These biochemical validation methods have been used in previous studies on smoking cessation [19, 20]. For subjects on nicotine replacement therapy, biochemical validation will be conducted 7 days after the completion of therapy.

### Outcomes

The primary outcome is biochemically validated smoking abstinence at 12 months.

Secondary outcomes are: (i) self-reported 7-day point prevalence of smoking abstinence at 6 and 12 months, (ii) self-reported reduction of ≥50% in cigarette consumption at 6 and 12 months, and (iii) any behaviour change as indicated by the subjects.

### Data analysis

The SPSS for Windows (version 25) will be used to conduct data analysis. We will first compare the baseline characteristics of the 2 groups using chi-square test for categorical variables and student t-test or Wilcoxon rank-sum test for continuous variables. The primary analysis will be the effect size of the intervention at 12 months. It will be estimated by the odd ratios (ORs). Crude ORs for quitting at 12 months will be estimated using logistic regression model and compared with ORs adjusted for potential or confirmed confounding baseline variables. The difference in biochemical validation quit rates at 12-month follow-up between intervention and control groups will be determined using Pearson’s chi-square test or with the use of Fisher’s exact test. Independent samples t-test will be used to determine whether there are statistically significant differences in length of abstinence for quitter between the intervention and control groups at 6 and 12-month follow-ups. The approach of intention-to-treat will be adopted. Those who are lost to follow-up or refuse to participate in the validation tests, will be treated as smokers with no reduction in cigarette consumption compared with (a) baseline, as the main analysis (by intention to treat), (b) the most recent level and (c) complete case (per protocol) analysis by excluding subjects with missing data as sensitivity analyses. Also, the number of communications with the subjects using WhatsApp/WeChat will be documented and analysed. In particular, all posts in the WhatsApp/WeChat will be archived. Each post will then be coded by 2 researchers independently, and will be classified by their content. Mann-Whitney U test will be applied to compare the median number of posts between the experimental and control group.

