#### Incorporating foot-in-the-door technique and brief MI to initiate a personalized general health promotion using information communication technology

The foot-in-the-door technique will be incorporated into the conceptual basis of the intervention to facilitate the recruitment process and enhance compliance of smokers. According to previous studies, most smokers with chronic diseases have had no intention to quit [5–7]. However, they were found to be interested in promoting their health [12, 13]. Through asking these smokers to identify, change and engage in their desirable health-related behaviours (a smaller and easier request), it is expected that they will be more motivated to quit smoking (a larger request) in later time.

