### Subjects

Hong Kong Chinese smokers with chronic diseases who have medical follow-up in a SOPC and fulfil the following inclusion criteria will be invited to participate: (1) aged 18 years or above, (2) able to speak Cantonese and read Chinese, (3) no intention to quit smoking (pre-contemplation stage), but are willing to take action to promote health, (4) have a smart phone and able to use instant messaging tool (e.g. WhatsApp, WeChat) for communication, and (5) willing to receive health promotion advices via WhatsApp/WeChat in the smart phone throughout the study. The exclusion criteria are: (1) unable to give informed consent or participate in our intervention due to impaired mental status, cognitive impairment, or communication barrier, and (2) participation in other smoking cessation programmes or services.

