### Sample size calculation

To determine the efficacy of using a personalized general health promotion approach in promoting smoking cessation for smokers with chronic diseases, we will recruit 60 smokers (30 in the intervention and 30 in the control groups) having medical follow-up in a SOPC in this study.

Power analysis will not be adopted for calculating the sample size as we have found no similar intervention in the literature. However, with the available resources and the proposed timeframe, we will be able to recruit 60 subjects. We therefore propose to have the sample size of 60 for this study, with 30 in the experimental group and 30 in the control group.

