#### Assessment for readiness to quit at 3-month follow-up

Although subjects do not have an intention to quit smoking at baseline (one of the inclusion criteria), the readiness of quitting smoking will be assessed at 3-month follow-up. For those who are willing to take further actions to promote their health, i.e. with an intention to quit smoking, health advice on smoking will be given with more emphasis on the health benefits of quitting. Upon request by subjects, we shall provide them with more comprehensive information on quitting. Specifically, the intervention should address the needs of smoking patients by teaching them with the skills to overcome withdrawal symptoms or cigarette cravings. In addition, subjects will be allowed to select their own schedules of quitting, such as to quit immediately or progressively. Our previous randomised controlled trial on the effectiveness of a self-determination intervention for smoking cessation (immediate or progressive) among people attending emergency departments showed that by giving autonomy for smokers to select their own schedules of quitting would enhance their self-efficacy and competence in quitting smoking. For those who request nicotine replacement therapy (NRT) to assist them quitting, we shall refer them to a smoking cessation hotline in which free sample of NRT will be offered. The whole intervention will be given to the subjects through WeChat/WhatsApp during the process of the study. However, we understand that older people always appreciate regular phone conversations intermingled with message. Hence, there will be a follow-up telephone call with our subjects each month for the first 6 months so as to further build a closer relationship with them.

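### Length of abstinence is to be t-tested among quitters only, a group formed after randomisation, so the result has no causal reading and can hide or reverse a benefit

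*Protocol article*

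**What the plan says.** All references are to the protocol article.

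- **Data analysis** fixes the test and its purpose: "Independent samples t-test will be used to determine whether there are statistically significant differences in length of abstinence for quitter". The comparison is of "differences in length of abstinence for quitter between the intervention and control groups at 6 and 12-month follow-ups". Nothing there marks it as descriptive or exploratory. The next sentence reads "The approach of intention-to-treat will be adopted", and the section then explains that subjects lost to follow-up or refusing validation are counted as smokers with no reduction.
- **Subjects** admits only smokers with "no intention to quit smoking (pre-contemplation stage), but are willing to take action to promote health".
- **Outcomes** states: "The primary outcome is biochemically validated smoking abstinence at 12 months". The three secondary outcomes are self-reported 7-day abstinence, a reduction in consumption of at least half, and any behaviour change the subject indicates. Length of abstinence is not among them.
- **Conceptual framework**, on the foot-in-the-door technique, describes engaging in another health behaviour first, after which "it is expected that they will be more motivated to quit smoking (a larger request) in later time". In the intervention arm "the readiness of quitting smoking will be assessed at 3-month follow-up", and advice stressing the benefits of quitting follows for those then willing.
- **Intervention group, In SOPCs** lists smoking reduction or quitting among the goals a subject may choose at baseline.
- **Sample size calculation**: "we will recruit 60 smokers (30 in the intervention and 30 in the control groups". The number rests on resources and timeframe; no quit rate is given.

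**The concern.** Nobody is a quitter at randomisation. If the intervention works, the intervention arm's quitters are a mixture of people who would have stopped anyway and people who stopped because of the intervention. The control arm's quitters are only the first kind. Restricting the test to quitters compares two differently selected groups, so the protection of randomisation is lost.

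The direction of the distortion depends on when the induced quitters stop and how long they last. If they tend to stop later, they have had less time to accumulate abstinence by 6 or 12 months, and an effective intervention can appear to shorten abstinence. If they stop at the same times as the others, the comparison shows nothing although more people have quit. The article says a larger trial is to follow from these findings, so a reported finding of shorter abstinence, or of no difference, could mislead its planners.

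The numbers are a second weakness. A t-test on a bounded duration, in the few quitters expected from 30 per arm, is fragile where it can be run at all.

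**Working it through.** The plan states no figure to reproduce. Quit rates and durations below are assumptions; only the 30 per arm comes from the document.

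**1. Quitters-only difference against the all-randomised difference**

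Let pc and pi be the quit rates in control and intervention, L0 the mean length among those who would quit anyway, and L1 the mean length among induced quitters. Suppose the intervention does not change length in the first group.

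- Mean among intervention quitters = [pc × L0 + (pi − pc) × L1] / pi
- Quitters-only difference = [(pi − pc) / pi] × (L1 − L0)
- All-randomised difference, non-quitters scored 0 = (pi − pc) × L1

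When pi exceeds pc, the all-randomised difference is positive. The sign of the quitters-only difference depends only on whether L1 is above or below L0.

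**2. Illustration at 12 months.** Assume pc = 5%, pi = 15% and no relapse after the quit date.

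- Would-quit-anyway subjects: quit dates uniform over months 0 to 12, so L0 = 12 − 6 = 6.0 months.
- Induced quitters: quit dates uniform over months 3 to 12, so L1 = 12 − 7.5 = 4.5 months.
- Mean among intervention quitters = (5 × 6.0 + 10 × 4.5) / 15 = 5.0 months.
- Quitters-only difference = 5.0 − 6.0 = **−1.0 month**.
- Per randomised subject: control 0.05 × 6.0 = **0.30**; intervention 0.15 × 5.0 = **0.75** months.

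**3. Sensitivity to the assumed quit dates and durations**

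| Rates | L0, L1 (months) | Quitters only | All randomised |
|---|---|---|---|
| 5% vs 15% | 6.0, 6.0 (both uniform 0–12) | 0 | 0.90 − 0.30 = +0.60 |
| 10% vs 20% | 8, 3 | 5.5 − 8 = −2.5 | 1.10 − 0.80 = +0.30 |
| 10% vs 20% | 8, 8 | 0 | 1.60 − 0.80 = +0.80 |
| 10% vs 20% | 6, 9 | 7.5 − 6 = +1.5 | 1.50 − 0.60 = +0.90 |

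The quitters-only figure is negative, zero or positive while the intervention is beneficial throughout.

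**4. Number of quitters available.** With X ~ Binomial(30, p), P(X ≥ 2) = 1 − (1 − p)^30 − 30p(1 − p)^29. This gives 0.227 at 3%, 0.446 at 5%, 0.816 at 10%, 0.952 at 15% and 0.989 at 20%. The chance that both arms have at least 2 is the product:

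- 3% vs 10%: 0.227 × 0.816 = 19%
- 5% vs 10%: 0.446 × 0.816 = 36%
- 5% vs 15%: 0.446 × 0.952 = 43%
- 10% vs 20%: 0.816 × 0.989 = 81%

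Two per arm is the least that gives each arm a variance estimate. A pooled-variance t-test would return a value with one quitter in one arm, but only by borrowing the other arm's variance. With no control quitters there is no test at all; that chance is 0.97^30 = 40% at 3%, 0.95^30 = 21% at 5% and 0.90^30 = 4% at 10%. Expected quitters at 5% vs 15% are 30 × 0.05 = 1.5 and 30 × 0.15 = 4.5.

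**The case against.** Four points can be made for the plan.

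**It concerns no declared outcome.** This stands. The primary analysis is an odds ratio for validated abstinence with missing subjects counted as smokers, and the quitters-only test does not touch it. That limits the seriousness of the point.

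**A reader might infer that the test contradicts the stated intention-to-treat approach.** The text does not support this. The rule as spelled out in Data analysis says how to classify missing and unvalidated subjects for quitting and reduction; it does not address length of abstinence. There is tension, because the rule removes such subjects from the quitter group and gives non-quitters no value. The defect is selection after randomisation, not self-contradiction.

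**A reader might infer that induced quitters must stop later and so must show shorter abstinence.** This is also too strong. Subjects may choose quitting as their goal at baseline and receive motivational interviewing towards it from the start. The Background also reports frequent relapse, so current length at 12 months need not follow the order of first quit dates. The −1.0 month comes wholly from the assumed asymmetry in dates; with equal dates it is zero. What remains is that the 3-month readiness step and the expected order of change make later quitting plausible.

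**A significant wrong-way result would be uncommon.** In simulation of the 5% vs 15% scenario, the difference was negative in about 64% of trials with at least 2 quitters per arm, but significantly so in only about 6% of those, or about 3% of all trials. A figure near 18% needs the steeper assumption of 8 and 3 months with SD 2 (10% vs 20%). This lowers the practical risk, but it does not give the comparison a causal meaning.

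**Conclusion.** The concern holds in a limited form. The plan fixes a significance test that conditions on a post-randomisation outcome, and no other section repairs it. That conclusion needs no assumed rates: whatever the quit rates, a difference among quitters cannot be attributed to the intervention.

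Reversal and masking are possibilities, and their size rests on assumptions that the documents neither supply nor exclude. The range shown runs from −2.5 to +1.5 months among quitters, against gains of +0.30 to +0.90 months per randomised subject. The chance of at least 2 quitters in each arm, about 19% to 81%, likewise depends on assumed rates from 3% vs 10% to 10% vs 20%.

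The impact is modest. It would be wrong to infer that the trial's main result is at risk: the primary odds ratio and the listed secondary outcomes do not depend on this test.

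**What to change.** Drop the t-test. Report length of abstinence among quitters descriptively by arm at 6 and 12 months (number of quitters, median and range), with no p-value and a note that the groups are not randomised.

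If a between-arm inference is wanted, define current length of abstinence at 6 and 12 months for all randomised subjects, scoring those not abstinent or missing as 0 in line with the missing-as-smoker rule. Compare the arms with a permutation or rank test, or give the mean difference with a bootstrap interval.

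The cost is a sentence or two of analysis wording. Length of abstinence is already planned for analysis, although the article does not say how quit dates are recorded, and that should be confirmed. The all-randomised version has drawbacks: with mostly zeros it is driven largely by the quit rate and so overlaps with the primary outcome, and it gives no credit for earlier abstinence in those who relapse. The descriptive report alone would be sufficient.

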### Ethical consideration

This study was approved by the institutional Review Board of the Hospital Authority of New Territories West Cluster (reference: NTWC/REC/19001), and was registered on the ClinicalTrials.gov (reference: NCT03983330). During subject recruitment, all eligible smokers who are willing to participate will be briefed on the purpose, design, procedures, potential benefits and risks of the study. Written consent will then be obtained.

### Patient and public involvement

Patients and public will not be included in the development, design, implementation or dissemination of the research. The results will be disseminated to the subjects through patient forums.

## Discussion

To the best of our knowledge, this is the first study to determine the potential efficacy for the use of a personalized general health promotion approach in promoting smoking cessation for smokers with chronic diseases. In fact, using brief advice or counselling was the most common smoking cessation intervention for smokers with chronic diseases [5, 7, 8]. Although such brief interventions are more feasible in busy clinical settings, they may not strong enough to make a significant impact on smokers with chronic diseases [8], especially most of them do not have any intention to quit and with a long smoking history [5–7]. Hence, there is an imperative need to develop an innovative method to assist smokers with chronic disease to achieve abstinence.

This study has several strengths. Firstly, previous studies indicated that smoking was likely to coexist with other risk behaviours [9–11]. Smokers usually engaged in other unhealthy habits, i.e. physical inactivity, alcohol drinking and unhealthy diet [21]. If our proposed intervention is effective, we will able to assist smokers with chronic disease to quit smoking and change their health behaviour simultaneously. This can have a significant effect on health care because we will help improve the physical well-being of smoking patients and eventually save more lives. Secondly, although a majority of smokers with chronic disease do not intend to quit smoking and refuse to join any smoking cessation intervention [5–7], they are willing to improve their health [12, 13]. If this intervention approach is feasible, we will be able to build and maintain rapport with these smokers through providing advices on how to change their desirable health behaviours. Once they are prepared for quitting, we can then deliver smoking cessation advices. Thirdly, our proposed intervention will be delivered using information communication technology. In comparison to the face-to-face method, which is known to be time-consuming and labour-intensive, our results will generate evidence to support the use of information communication technology to deliver brief motivational interviewing to promote smoking cessation. The sustainability of this inexpensive method will be ensured as it can reach many smokers at a low cost. Besides, based on the findings of this randomised controlled trial, a large randomised controlled trial will be conducted to evaluate the effectiveness and costs of a personalized general health promotion approach in promoting smoking cessation for smokers with chronic diseases in the future.

## Data Availability

Not applicable.

## Abbreviations

SOPC: Special Out-Patient Clinics
MI: Motivational interviewing
SNOSE: Serially Labelled, Opaque and Sealed Envelope
NRT: Nicotine Replacement Therapy
ORs: Odd Ratios
